## Abstract

**Background:**

Adjuvant endocrine therapy can improve disease**-**free survival and time before recurrence in breast cancer patients. However, it is associated with considerable side effects that negatively affect patients’ quality of life and cause non**-**adherence. The recently demonstrated effect of individual expectations on side**-**effect development (nocebo effect) suggests that psychological factors play a role in the prevention of side effects. The aim of this study is to evaluate cognitive**-**behavioral side**-**effect prevention training (SEPT) for breast cancer patients. This article describes the study protocol and applied research methods.

**Methods/Design:**

In a randomized controlled trial, 184 female breast cancer patients are assigned to receive either SEPT, standard medical care or a manualized supportive therapy at the start of adjuvant endocrine treatment. SEPT consists of three sessions of cognitive**-**behavioral training including psychoeducation to provide a realistic view of endocrine therapy, imagination**-**training to integrate positive aspects of medication into daily life, and side**-**effect management to enhance expectations about coping ability. Side effects three months after the start of endocrine therapy serve as primary outcomes. Secondary outcomes include quality of life, coping ability and patients’ medication adherence. Patients’ expectations (i.e., expectations about side effects, coping ability, treatment and illness) are analyzed as mediators.

**Discussion:**

The optimization of expectations might be a potential pathway in health care to improve patients’ quality of life during long**-**term medication intake. The results will provide implications for a possible integration of evidence**-**based prevention training into clinical practice.

**Trial registration:**

ClinicalTrials.gov, (NCT01741883).

## Background

Endocrine therapy is the pivotal adjuvant treatment for over 75% of breast cancer patients. National and international guidelines recommend it for long**-**term intake, over at least five years, in patients with hormone**-**receptor**-**positive primary breast cancer [1,2]. Adjuvant endocrine therapy reduces the risk of cancer recurrence, development of metastases, and cancer mortality [3,4]. Despite these benefits, almost every second patient discontinues treatment [5], while another 17% refuse to initiate drug intake [6]. Reported non**-**adherence rates range from 35% to 50% [7,8], leading to increased mortality in women with breast cancer [9]. Main reasons for non**-**adherence are side effects that reduce patients’ quality of life [10]. Thus, effective side**-**effect management and side**-**effect prevention are crucial.

Most frequently reported side effects of endocrine therapy are arthralgia, hot flushes, weight gain, mood swings, loss of libido and vaginal dryness [11,12]. To a great extent these symptoms are directly caused by the pharmacodynamics of the treatment, depleting women of female sex hormones, thereby initiating or adding up to typical menopausal discomforts. In contrast, long**-**term evaluations of adjuvant hormonal therapy showed that a substantial proportion of the reported side effects were not related to the treatment [13]. These side effects, such as headaches, skin irritation, dizziness, nausea and gastrointestinal irritation, have no known pharmacological association with endocrine treatment and are therefore termed non**-**specific medication side effects [14]. They are influenced by patient characteristics such as expectations and pre**-**existing symptoms. It is assumed that analog processes are involved in the nocebo (Latin: “I shall harm”) phenomenon, in which placebo**-**pills cause adverse effects [15]. Hence, a randomized placebo**-**controlled study of letrozole showed that around 20% of breast cancer patients in the placebo arm experienced typical menopausal symptoms [16]. Thus, negative expectations can not only influence the occurrence of non**-**specific side effects but even worsen specific side effects via the nocebo**-**mechanism (nocebo effect) [17,18].

Negative expectations about medication have been shown to predict the incidence of non**-**specific side effects in patients with rheumatoid arthritis, even if disease severity and medication regimen were controlled [19]. Expectations about occurrence and intensity of side effects seem to be an important predictor of side effects in cancer treatment [20], for example chemotherapy**-**related nausea [21]. A recent meta**-**analysis showed a significant, medium**-**sized association between patients’ expectations of side effects and the actual experience of these side effects from cancer treatments [22]. In a pilot study by our group, response expectations predicted the incidence of side effects three months after the start of endocrine treatment [23,24]. Furthermore, cognitive representations and expectations about the consequences of illness were found to be associated with physical health outcomes in breast cancer patients [25]. Leventhal’s self**-**regulation model of health [26] additionally focuses on expected coping with illness [27] and the emotional representations of an illness [26]. Thus, anxiety [28] and depression may be relevant in the development of nocebo effects and non**-**specific side effects [14]. Several other factors appear to be of importance in this context: e.g., prior experiences with side effects [22], higher pre**-**existing symptoms [29], and the tendency toward somatization, symptom amplification and selective attention on bodily sensations [14], all of which can result in a possible misinterpretation of prior existing symptoms as side effects of the cancer medication [30]. Taken together, patients’ expectations seem to be essential for the development of side effects. Optimizing these expectations might be a promising way to minimize patients’ side**-**effect burden during long**-**term intake of endocrine medication.

Only few studies have tried to optimize expectations in cancer treatment. Changes in illness representations are associated with less fear of progression [31], and patients with high expectations for treatment**-**induced nausea could profit from a positive expectation**-**manipulation [32]. In particular, the way information about side effects is given to the patients is crucial for the development of expectations. It is recommended that information be framed in a positive way, e.g., not only explain possible side effects but also the expected benefits of the medication. Further, it is important to promote a positive doctor**-**patient interaction and to foster effective management of symptoms [33]. Recent studies showed that cognitive behavioral therapy helps breast cancer patients in the management of menopausal side effects and can lead to decreased levels of reported symptoms [34,35]. So far, no study has focused on optimizing expectations to prevent side effects. We therefore developed a psychological side**-**effect prevention training (SEPT) to prevent side effects by optimizing patients’ expectations, which may be an effective pathway to enhance overall quality of life. This article describes the study design and the research methods to answer the following research questions:

 1. Is a three**-**session psychological intervention effective in reducing side effects and improving quality of life during long**-**term intake of endocrine therapy?

 2. Do treatment and side**-**effect expectations mediate the beneficial effects?

 3. Are there certain patient characteristics that predict which patients benefit the most from the training?

## Methods/Design

### Study design

The study is designed as dual**-**center, randomized controlled trial with three arms and follow**-**up assessment (see Figure 1). The study procedure is implemented at the Department of Gynecology, Gynecological Endocrinology and Oncology, Philipps University Marburg, Germany, and at the University Medical Center Hamburg**-**Eppendorf, Germany. Participants are women with hormone**-**receptor**-**positive breast cancer, scheduled to start adjuvant endocrine treatment. After signing informed consent to participate in the study and receiving medical information about endocrine treatment from the hospital staff, all patients are provided additional standardized information and patient education about the scheduled treatment by a trained research assistant/ clinical psychologist to homogenize knowledge about endocrine treatment. The structured treatment information is given verbally and through a leaflet, illustrating the physical mode of action, the desired effects, and the potential side effects of endocrine therapy. After completing baseline assessment (including symptom status and pre**-**treatment side**-**effect expectations) patients are randomly assigned to one of three groups. Group 1 receives standard medical care (SMC) only. Group 2 receives SMC and the side**-**effect prevention training (SEPT). Group 3 receives SMC and supportive therapy as an attention control group (ACG). Outcomes are assessed homogeneously in all three groups, three and six months after the start of medication intake.

**Figure 1 F1:**
[figure not shown]
Study design.

### Participants

Patients with hormone**-**receptor**-**positive primary breast cancer scheduled to undergo first**-**line endocrine treatment with tamoxifen (and additional GnRH**-**analoga, depending on the menopausal status) or a third**-**generation aromatase inhibitor (i.e., anastrozole, letrozole or exemestan) are eligible. Exclusion criteria are the presence of a serious co**-**morbid psychiatric condition (schizophrenia, addiction, severe affective or severe anxiety disorder), the presence of a life**-**threatening co**-**morbid (non**-**cancer) medical condition, insufficient German language skills, and cognitive inability to give informed consent. Inclusion and exclusion criteria are checked by screening patients’ history and medical records and standardized assessment using the structured psychiatric interview “mini**-**dips” [36].

### Recruitment and informed consent

Diagnosis and treatment are initiated independently of the study according to the German breast cancer guidelines by the interdisciplinary tumor board of the breast cancer center. Patients are required to have completed primary surgery and/or chemotherapy, if indicated.

Patients are screened for eligibility during their hospital stay in the breast cancer center. Women meeting the inclusion criteria are informed about the study concept and invited by their oncologists to take part in the study. Patients who give written informed consent after receiving detailed written and verbal information are admitted to the study. Participation is voluntary and can be withdrawn by the patient any time with no disadvantages.

### Ethics

The study protocol was approved by the medical ethics committee of the Philipps University Marburg, and the Hamburg Medical Chamber. The study will be conducted in accordance with the Declaration of Helsinki, Good Clinical Practice guidelines, including data and patients’ privacy protection.

### Sample size calculation

Required sample sizes were determined a priori with G**-**Power [37]: The sample size for the randomized group comparison was determined according to a MANOVA with repeated measures, testing for a three groups x three time points interaction. Assuming a medium effect size of f(V)=.20, N=153 patients (n=51 per group) are needed to achieve 80% power.

Taking into account a potential drop**-**out rate of 20% (e.g., due to exhaustion or medical complications), we aim to include a total of 184 breast cancer patients.

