### Quality standards (Minimization of bias)

#### Randomization and blinding

Randomization follows after completing baseline assessment. Patients are equally allocated to one of the three treatment arms using sealed envelopes. Assignment follows a stratified permuted block randomization procedure with a block size of nine. Stratification criteria (2×2) are the sum score (≤13 vs. >13) of the hospital anxiety and depression questionnaire (HADS**-**D) [38,39] during hospital stay and type of medication (aromatase inhibitor vs. tamoxifen). Assignment sequence is generated by staff who are not involved in the intervention process and conducted electronically using the statistical program WINPEPI [40]. The research assistants responsible for the assessment are blinded to group allocation.

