### Data analysis

Missing values will be replaced using multivariate imputation techniques. A repeated measures multivariate analysis of variances (MANOVA) will be used to analyze treatment effects. To identify predictors of treatment outcome, multiple regression analyses will be conducted. To analyze pathways of the effects, mediator analyzes will be computed. Case studies will be performed to illustrate characteristics of the treatment processes from patients’ und therapists’ perspectives. Level of significance will be set at α = .05.

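### The 20% drop-out allowance multiplies 153 by 1.20 instead of dividing by 0.80, so 184 enrolled leaves 147 completers, not 153 (minor arithmetic error)

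*Protocol article*

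**What the plan says.** All the figures stand in the Protocol article under Sample size calculation. The calculation is for a "MANOVA with repeated measures, testing for a three groups x three time points interaction". The effect is given as "Assuming a medium effect size of f(V)=.20", and the result as "N=153 patients (n=51 per group) are needed to achieve 80% power". The section then allows for a possible drop-out "rate of 20% (e.g., due to exhaustion or medical complications), we aim to include a total of 184 breast cancer patients". The abstract repeats 184 as the number of patients. The article gives no other drop-out rate and no other inflation rule.

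Two other places bear on the point. Under Attrition bias, all randomised patients are to be analysed by intention to treat. Under Data analysis, missing values are to be filled by multivariate imputation.

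**The concern.** The required number, the drop-out rate and the enrolment target are all printed in two sentences, and they do not fit together. If one fifth of 184 patients are lost, fewer than 153 complete. A reader would take the paragraph to mean that the trial can lose 20% and still have the patients it needs for 80% power. As printed, it has a smaller margin. A loss between about 17% and 20% would look within plan while leaving fewer than the 153 the section calls for.

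**Working it through.** **Inputs.**
- Required number: 153, or 51 per group, for 80% power (Sample size calculation).
- Effect size f(V) = 0.20, three groups by three time points (Sample size calculation).
- Drop-out 20%, target 184 (Sample size calculation).
- Alpha: "Level of significance will be set at α = .05" (Data analysis). The sample size section names no alpha, so using this one is an assumption.
- Allocation: "Patients are equally allocated to one of the three treatment arms using sealed envelopes" (Randomization and blinding).

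**Step 1: does 153 reproduce?** For the group-by-time interaction with 3 groups and 3 times, s = min(2, 2) = 2, df1 = 2 x 2 = 4 and df2 = 2(N - 3). Power comes from the noncentral F distribution. Two conventions for the noncentrality were tried:
- O'Brien-Shieh: lambda = 0.20² x 2 x N = 0.08N
- Muller-Peterson (the alternative): lambda = 0.20² x df2 = 0.08(N - 3)

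| N | Power, O'Brien-Shieh | Power, Muller-Peterson |
|---|---|---|
| 147 | 78.6% | 77.6% |
| 152 | 80.1% | 79.2% |
| 153 | 80.4% | 79.5% |
| 184 | 88.0% | 87.4% |

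The smallest N for 80% is 152 under the first convention, and the next multiple of three is 153. The plan's base number therefore reproduces. Under the second convention the smallest N is 155.

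**Step 2: where does 184 come from?**
- 153 x 1.20 = 183.6, rounded up to 184. This matches the plan.
- 153 / (1 - 0.20) = 191.25, so 192 with equal arms (64 per arm). This does not match; the difference from 184 is 8 patients.

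**Step 3: what does 184 deliver?**
- At 20% drop-out: 184 x 0.80 = 147.2, so 147 completers, or 49 per group. The shortfall is 153 - 147 = 6.
- Largest loss that still leaves 153: 1 - 153/184 = 31/184 = 16.8%.
- Check on 192: 192 x 0.80 = 153.6, which leaves 153.

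**Step 4: power at 147.** From the table, 78.6%, or 77.6% under the alternative convention. Relative to N = 153 the loss is 80.4 - 78.6 = 1.8 points, or 79.5 - 77.6 = 1.9 points.

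**The case against.** **The effect is very small.** This stands. Against the 80% target the shortfall is 80 - 78.6 = 1.4 points under the convention that reproduces 153. The two conventions themselves differ by 0.9 points at N = 153 (80.4% against 79.5%). Both gaps are small beside the uncertainty in a conventional medium effect size. This sets the grade of the finding, but it does not make the paragraph correct.

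**Drop-outs stay in the analysis.** The section does not say that the 153 must be completers, and the plan analyses everyone randomised, with imputation. Patients who leave early still contribute baseline and any earlier assessments, so 147 is a conservative count and the true loss may be smaller. That much stands. But imputation does not recover outcomes that were never observed, and the section itself treats drop-out as a loss, since otherwise it would need no allowance. If all 184 counted in full, power would be about 87-88%, which is not what the section claims either. Neither reading reconciles the three numbers.

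**The 20% could mean 20% of 153.** That would explain 184. But the text speaks of a drop-out "rate of 20% (e.g., due to exhaustion or medical complications"), and these things happen to patients already enrolled. The natural denominator is those enrolled.

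**The wording is planning language.** The drop-out is called potential and the 184 an aim. This is fair, but an allowance for a stated rate should still cover that rate.

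A reader might also infer that the trial is materially underpowered, that the base calculation is wrong, or that 192 patients must be recruited. The documents support none of these. The base number reproduces, the power loss is about 2 points at the planned drop-out, and up to 16.8% loss the required 153 remain.

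**Conclusion.** The paragraph is wrong as written, and the error is minor. The allowance was applied as a 20% addition to 153 instead of dividing by the 80% retained. At the stated drop-out, 184 gives 147 completers (49 per group), 6 fewer than the 153 required, with power about 78.6% (77.6% under the alternative formula) instead of 80%.

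The counts rest only on the section's own figures and on reading drop-out as a share of those enrolled. The power figures also assume alpha = 0.05, f(V) = 0.20, equal groups and an analysis of completers only. How far imputation would soften the loss cannot be worked out from the article. No analysis, outcome or trial procedure is affected.

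**What to change.** Correct the sentence and leave the enrolment target at 184. State that 184 enrolled leaves the required 153 patients only if drop-out is at most 16.8%. State also that at 20% drop-out 147 remain (49 per group), with about 78-79% power for the interaction test (77.6% under the alternative noncentrality formula). Show the inflation as N / (1 - drop-out), so that the reader can see that full cover for 20% would be 153 / 0.80 = 191.25, or 192.

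It is safer to tie the 16.8% to the 153 patients than to 80% power: under the alternative formula 153 gives 79.5%, and under the main one 152 already suffices. A short note that the figure is completer-based, while the analysis includes all randomised patients with imputation, would complete it.

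The cost is a sentence or two in one section. The stated drop-out cover becomes slightly less favourable, and nothing else changes.

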### Quality standards (Minimization of bias)

#### Randomization and blinding

Randomization follows after completing baseline assessment. Patients are equally allocated to one of the three treatment arms using sealed envelopes. Assignment follows a stratified permuted block randomization procedure with a block size of nine. Stratification criteria (2×2) are the sum score (≤13 vs. >13) of the hospital anxiety and depression questionnaire (HADS**-**D) [38,39] during hospital stay and type of medication (aromatase inhibitor vs. tamoxifen). Assignment sequence is generated by staff who are not involved in the intervention process and conducted electronically using the statistical program WINPEPI [40]. The research assistants responsible for the assessment are blinded to group allocation.

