#### Control for therapeutic allegiance

To ensure the comparability of treatments, treatment dose, application and assessment occasions for SEPT and ACG will be identical.

All therapists are clinical psychologists with advanced cognitive behavioral training and have comparable professional experience. They are trained in the use of the treatment manual before the trial starts. Training includes a full treatment cycle with at least one patient per treatment group using video feedback and professional supervision of each treatment session. During the whole study therapists are under ongoing supervision by highly experienced psycho**-**oncologists. Both types of interventions are manualized and each therapist will treat a comparable number of patients in each group. Treatment fidelity is assessed and rated before approval of therapists to start in this trial. All sessions will be videotaped and an amount of 33% will be selected randomly and rated by an independent rater.

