### Baseline demographic data

Preliminary baseline demographic data was assessed in N = 55 participating women with a primary breast cancer diagnosis. On average patients were 54.8 years old (SD=8.2, range=39-71 years), and mostly married or living with a partner (61.8%). Other patients were single (12.7%), widowed (5.5%) or divorced (20.0%). The majority of patients had primary education (63.6%), other patients finished secondary education (16.4%) or university education (20.0%).

More than half of the patients were diagnosed with stage I breast cancer (69.1%), further 27.2% of patients were diagnosed with stage II and additional 3.6% with stage III. Most patients (89.1%) received breast conserving therapy and only 10.9% mastectomy. A large group of patients (69.1%) was scheduled to undergo first-line endocrine treatment with tamoxifen (+/− GnRH-analoga). A third generation aromatase inhibitor (i.e. anastrozole, letrozole or exemestan) was recommended to the other patients (30.9%).

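### A single published block size of nine makes up to one assignment in seven predictable to anyone who can follow a stratum's list; varying the unopened blocks would be a cheap improvement

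*Protocol article*

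**What the plan says.** The Randomization and blinding section fixes the scheme: "Patients are equally allocated to one of the three treatment arms using sealed envelopes", and then "Assignment follows a stratified permuted block randomization procedure with a block size of nine". No other size is mentioned, and nothing says that the size varies or is withheld. Four strata are defined: "Stratification criteria (2×2) are the sum score (≤13 vs. >13) of the hospital anxiety and depression questionnaire", crossed with "type of medication (aromatase inhibitor vs. tamoxifen"). The HADS score is the one taken in hospital and the drug is already scheduled, so a woman's stratum is known before she is randomised.

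The same section contains three safeguards. The sequence is generated electronically by staff outside the intervention, randomisation comes after baseline, and the assessing research assistants are blinded. No one else is said to be blinded. Under Control for therapeutic allegiance, each therapist treats patients in both active arms; under Study design, the third arm has standard care only.

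Several steps precede randomisation. Oncologists invite eligible women (Recruitment and informed consent). Psychiatric exclusions are checked from records and with a structured interview (Participants). Standardised treatment information is given "by a trained research assistant/ clinical psychologist to homogenize knowledge about endocrine treatment" (Study design).

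The Baseline demographic data section reports 55 women so far, against a target of 184 under Sample size calculation. The block size therefore became public with most of the planned sample apparently still to be randomised.

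**The concern.** In a permuted block of one known size, the last places are determined by the earlier ones. With three places per arm, the ninth is always certain to someone who has followed the list, and the eighth and seventh sometimes are. Therapists know which active treatment each of their patients receives, and patients can at least tell sessions from no sessions, so past assignments do not stay hidden after the envelope is opened.

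The outcome is sensitive to who enters which arm. The primary measure is patient-rated symptom intensity on the GASE, and the article's Background links side effects to expectations, anxiety, depression and pre-existing symptoms. Staff may see these before randomisation, and stratifying on one HADS cut-off captures them only partly. If the timing or fact of enrolment were influenced by a foreseen arm, the comparison of SEPT with its controls would no longer be protected by randomisation.

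**Working it through.** The article gives no figure for predictability, so there is none to reproduce.

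**Inputs from the article.** Block size 9; three arms, equal allocation, hence 3 places per arm per block; four strata; 184 women in total. For stratum sizes: "A large group of patients (69.1%) was scheduled to undergo first-line endocrine treatment with tamoxifen", so 30.9% on an aromatase inhibitor.

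**Assumptions.** The HADS split is not given; splits from 50/50 to 90/10 are used. Whether the two centres share lists is not stated; four lists (shared) and eight lists (each stratum halved between centres) are both shown. The observer knows the block size and all earlier assignments in the list.

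**Step 1: one complete block.** An assignment is certain when only one arm has places left.
- Place 9: probability 1.
- Place 8: the last two places belong to the same arm, 2/8 = 1/4.
- Place 7: the last three belong to the same arm, (2/8)(1/7) = 1/28.
- Places 1 to 6: probability 0.

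The expected number of certain assignments per block is 1 + 1/4 + 1/28 = 36/28 = 9/7 = 1.286. The share is (9/7)/9 = 1/7 = 14.3%. Enumerating the block also shows that at least one arm is ruled out for 35.7% of assignments, and that a best guess is right 53.2% of the time, against 33.3% by chance.

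**Step 2: 184 women, with unfinished last blocks.**
- Four equal lists of 46: 46 = 5 × 9 + 1, so 5 × 9/7 = 6.43 per list and 4 × 6.43 = 25.7 in total; 25.7/184 = 14.0%.
- HADS split 60/40: lists of 76, 51, 34 and 23 contain 8 + 5 + 3 + 2 = 18 complete blocks. 18 × 9/7 = 23.14, plus 1/28 for the seventh place of the open block in the list of 34, gives 23.2, or 12.6%.
- All splits from 50/50 to 90/10, four lists: 12.6–14.0%, about 23–26 women.
- Eight equal lists of 23: 23 = 2 × 9 + 5, so 8 × 2 × 9/7 = 20.6, or 11.2%.
- All splits, eight lists: 11.2–12.9%, about 21–24 women.

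**Step 3: effect of varying the block size.** Simulation of a list of 46, with sizes drawn at random and an observer who knows the set of sizes but not their order:

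| Sizes | Known with certainty | Best guess correct |
|---|---|---|
| 9 only | 13.9% | 53% |
| 6, 9, 12 | 2.3% | 52% |
| 3, 6, 9 | 3.5% | 55% |
| 9, 12, 15 | 1.8% | 50% |

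A guess of SEPT is 0.29 more probable at a true SEPT place than at another place with fixed nines. With 9/12/15 the difference is about 0.24–0.25, depending on the run; with 6/9/12 it is 0.28, almost unchanged. Mixing in blocks of three makes guessing easier.

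**The case against.** The strongest reply is that the prediction needs knowledge that no recruiter is shown to have. Oncologists invite patients, blinded research assistants administer the questionnaires at every time point including baseline, and independent staff generate the sequence. Therapists know the arm but are not described as enrolling anyone. This stands, and it makes the 11–14% an upper bound.

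A reader might infer more: that one psychologist team follows all three arms, that envelopes lie in the clinics, or that those who inform patients before randomisation are the therapists. The article does not say so. It states "All therapists are clinical psychologists with advanced cognitive behavioral training", and allows a clinical psychologist to give the pre-randomisation information, but neither identifies nor separates the two groups. Custody of the envelopes and separate centre lists are details that an article commonly leaves to the full protocol. It should also not be inferred that patients can tell SEPT from supportive therapy.

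The room for discretion is also limited. The psychiatric exclusion is backed by a structured interview, treatment is decided by the tumour board independently of the study, and consent and baseline precede assignment. These points reduce the opportunity, but whom to invite and when baseline is completed can still vary.

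Finally, the planned test is of a group-by-time interaction and the GASE is taken at baseline, so stable symptom differences largely drop out, and baseline HADS and expectations would help to reveal selection. That stands in part. Differences in anxiety or expectation that predict later change would not drop out.

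Nine is also not a small block: fixed blocks of 3 or 6 would make 1/3 or 1/5 of assignments certain.

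**Conclusion.** The point holds as a weakness of a stated design choice. One fixed block size, published during recruitment, allows at most 1/7 of assignments in complete blocks to be known in advance: about 11–14% of 184, or roughly 21–26 women, over the assumed HADS splits and with four or eight lists. This requires knowledge of the block size and of all earlier assignments in the list. Independent sequence generation protects the list itself; it does not stop someone counting down a known block.

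A reader might go on to conclude that the SEPT comparison is biased, or put a size on it by multiplying the guessing advantage of about 0.29 by a supposed difference between selected and other women. The documents do not support this. They give no such difference, the product assumes that every guess is acted on successfully, and nothing suggests that anyone has tried. The established part is the predictability, not its use. This is a cheap improvement, not a flaw that undermines the trial.

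**What to change.** For all blocks not yet opened:

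1. Have the same uninvolved staff regenerate the list in the same program with block sizes of 9, 12 and 15 in random order. Do not include blocks of three.
2. Withhold the new sizes from site staff and from documents open to them.
3. Open or release each assignment only after consent, eligibility, stratum and completed baseline have been logged. If the full protocol already requires this, nothing changes here.

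The cost is a new electronic list and, if release is not already handled this way, one call or e-mail per patient. The statistical price is a slightly larger possible imbalance in the last incomplete block of each stratum. Certain assignments become rare, but an observer who tracks the arms can still guess right about half the time, so the release rule matters as well as the block sizes.
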